**Fig. 1 Fig1:**
[figure not shown]
Flowchart of participants in the EUDAIMON study

### Interventions

#### *Intervention group* (TAU + MBSR; see Table 1)

**Table 1 Tab1:** Session outlines for Mindfulness-Based Stress Reduction (MBSR) group treatment protocol

Session	MBSR^a^
1	Recognising the present moment. Beginner’s Mind, Introduction to Programme, Foundations of Mindfulness, More right with you than wrong, Introduction to Body Scan meditation, Intake.
2	Engaging with the breath. Patience, Basic Training, Working with perceptions, The Wandering Mind, Mindful Yoga.
3	Practice, practice, practice. Non-Striving, Mindfulness of Breathing Meditation, Lying Yoga, Attention vs. Disattention, Pleasant Events.
4	Stress and the flow of emotions. Stressful Events, Responding vs. Reacting, Seeing Our Patterns, Sitting Meditation, Standing Yoga, Research on Stress & Stress Hardiness.
5	Stress and thoughts: finding another place to stand. Working with Thoughts & Emotions, Group Reflections on Halfway Point, Small & Large Groups, Sitting Meditation, and Qigong.
6	Interpersonal mindfulness/mindful communication. Mindfulness & Communication, Avoiding Difficulty vs. Entering and Blending, Loving kindness Meditation, Walking Meditation. Daylong Session^a^: Putting it All Together.
7	Applying mindfulness. Sitting Meditation, Qigong, Trust & Self-Reliance, Mindful Consumption, Making the Practice Your Own, Mindfulness in Everyday Life.
8	Making mindfulness a part of your life. Sitting Meditation, Walking, The Class Never Ends: Practice for the rest of Your Life, Course Evaluations, Group Reflection & Checking Out.

^a^NOTE: Daily home practice of 30–45 min. duration, 6 days per week is encouraged (home practice guided by a workbook and audiotapes). In accordance with the MBSR protocol developed at the University of Massachusetts Medical School, 1 day-long meditation retreat will be held between sessions 6 and 8 of the programme

We will use the MBSR protocol developed at the University of Massachusetts Medical School, USA. MBSR [47] is intensive, structured training in mindfulness meditation which aims to help patients increase their awareness of the present experience and to relate to their physical and psychological conditions in a more accepting and non-judgmental way. The standard MBSR programme consists of 8 weekly sessions of around 2.5 h each and homework for 45 min a day, 6 days a week, even though several modifications in sessions, homework, and total duration can be observed among distinct courses for various patient populations. MBSR usually has three main components including a “*body scan*”, which involves a gradual sweeping of attention through the entire body from feet to head, focusing non-critically on any sensation or feeling in body regions and using periodic suggestions of breathing awareness and relaxation; “*sitting meditation*” which involves both mindful attention to breathing or on the rising and falling abdomen as well as other perceptions, and a state of non-judgmental awareness of cognitions and of the stream of thoughts and distractions that continuously flow through the mind; and “*Hatha yoga*” practice, which includes breathing exercises, simple stretches, and postures designed to strengthen and relax the musculoskeletal system. In addition to in-class mindfulness exercises, participants are encouraged to engage in home mindfulness practice and attend an all-day intensive mindfulness meditation retreat. The main premise of MBSR is that with repeated training in mindfulness meditation, individuals will eventually learn to be less reactive and judgmental toward their experiences, and more able to recognise, and break free from, habitual and maladaptive patterns of thinking and behaviour. It is important to mention that MBSR is not directed at symptom reduction but more fundamentally towards altering how perceptible mental processes and content are experienced, towards greater awareness, acceptance, and tolerance of the unavoidable vagaries of life, which facilitate enhanced psychological wellbeing, even in the face of continued symptoms. The eight 2 h MBSR sessions (once a week) will be performed in groups (*n* = 15 per group) and will be led by four accredited MBSR instructors (one per group) that have undergone MBSR training, which will enable an analysis of possible instructor effect on the outcomes, as recommended by Öst [48]. A book with MBSR manual and CDs with guided mindfulness practice sessions will be provided to the participants. In addition, we will reinforce MBSR treatment adherence by inviting participants to use a Mindfulness smartphone app developed in 2014 at the University of Zaragoza, Spain. The app has been scientifically validated by the Aragon Institute of Health Sciences. It is the first app that tracks the state of mindfulness and provides feedback on how mindful the person is during mindfulness meditation sessions. It also provides instruction in several mindfulness techniques by means of well-designed videos and audio recordings.

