### Participants

A total of 180 FMS patients will be recruited from the Rheumatology service at Sant Joan de Déu Hospital (St. Boi de Llobregat, Spain). Sample size is established on the basis of a previous meta-analysis of controlled MBSR trials [45] in which a mean effect size of *d* = 0.53 was found. This effect size results in 1-b = 0.89 (alpha = 0.05) for *N* = 60 patients per group (180 patients overall). With 20 % maximal attrition, the power remains 1-b = 0.82. The estimated sample size for the study of biomarkers (neuroimaging and cytokines) was 30 participants per condition, this sample size is considered adequate given that approximately 20–40 participants (in between-group designs) are necessary to detect a change of 15 % in cerebral blood flow in regions of interest (ROI) by means of pseudo-continuous Arterial Spin Labeling (pCASL) [46].

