### Procedure

The potential FMS participants will be screened through an initial telephonic interview by one of the authors ([name]), who will provide a general overview of the study. Subsequently, two highly trained clinical psychologists (not involved with the treatment and blind to group allocation) will make an appointment with those patients who met the inclusion criteria and agreed to participate in the study. The psychologists will check all inclusion/exclusion criteria (both general and additional for the biomarkers study) and will perform all face-to face interviews. As mentioned above, study participants will be randomised to one of the three conditions (i.e., TAU, TAU + MBSR, TAU + FibroQoL). Both MBSR and FibroQoL are conducted in a group format (up to 15 people in each group). To balance the number of participants eligible for the biomarkers sub-study across the three arms, stratified randomisation will be performed. The proportion of eligible participants for the biomarkers evaluation and those only meeting criteria for the general study will be pre-fixed at 1:1 in all samples. Four treatment waves (*N* = 45 each) will be carried out to achieve the required final sample (*N* = 180).

Three-five days after the clinical evaluation, patients assigned to the biomarkers sub-study will be contacted for blood extraction and MRI completion. To minimise circadian variability in immunological markers, all whole blood samples will be collected between 8–9 am. Interventions will be conducted using a parallel design to reduce seasonal variability in the study measures. The participants will be interviewed at baseline, after treatment, and at 12-month follow-up (56 weeks after randomisation). The neuroimaging tests and cytokine measurements will be performed at baseline and after treatment. A flowchart of participants is displayed in Fig. 1.

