#### Analysis of clinical efficacy

To assess treatment effects, we will perform Intention-to-Treat analyses, which will include all participants who undergo random allocation, using multiple imputation to replace missing values.

To study the differences in the primary outcome and in each of the secondary outcomes between groups, linear mixed-effects models [85] will be prepared using Restricted Maximum Likelihood to estimate the parameters. Comparisons amongst treatment groups at post-treatment and at 12-month follow-up will be computed with estimates derived from the linear mixed-effect models (use of the Bonferroni method to adjust the significance level of the pairwise contrasts). Calculations of between-groups effect sizes using Cohen’s *d* with its 95 % confidence interval will be based on the pooled standard deviation at baseline. Finally, to make the findings from the present RCT meaningful to clinicians, the number-needed-to-treat (NNT) [86] in the MBSR condition will be reported. Taking the Luciano et al. [87] NNT approach as our reference, we dichotomise participants into responders or non-responders using three separate cut-off criteria: (a) ≥ 20 % reduction on the FIQR total score from baseline to post-treatment; (b) ≥ 50 % reduction on the FIQR total score from baseline to post-treatment; and (c) number of patients crossing a cut-off point (reaching no worse than mild functional impairment; FIQR total score < 39).

Given that some pharmacological treatments may interfere with cytokine levels [88], differences in cytokine levels between patients taking vs. not taking antidepressants will be evaluated.

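### The stated power makes no allowance for therapy-group clustering, and with one instructor per MBSR group an instructor effect cannot be told apart from a group effect

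*Protocol article*

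**What the plan says.** **Delivery.** The section on the TAU + MBSR arm sets groups of 15. The leaders are to be "four accredited MBSR instructors (one per group) that have undergone MBSR training, which will enable an analysis of possible instructor effect". Under Procedure, "Both MBSR and FibroQoL are conducted in a group format (up to 15 people in each group"), and treatment runs in four waves of 45 patients. The FibroQoL section describes a group programme given by a team. It states neither the number of groups nor a separate leader for each.

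**Sample size (Participants).** From a meta-analysis, "a mean effect size of *d* = 0.53 was found". Then "This effect size results in 1-b = 0.89 (alpha = 0.05") for 60 "patients per group (180 patients overall"). The allowance for dropout reads: "With 20 % maximal attrition, the power remains 1-b = 0.82". No ICC, design effect or number of therapy groups enters.

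**Analysis (Analysis of clinical efficacy).** Linear mixed-effects models "will be prepared using Restricted Maximum Likelihood to estimate the parameters", with Bonferroni-adjusted pairwise contrasts. Neither random effects nor covariates are listed. The instructor analysis announced in the MBSR section does not reappear in the statistical sections.

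**The concern.** Patients treated together share a leader, peers and a calendar slot, so their outcomes tend to be correlated. This applies to MBSR and FibroQoL but not to TAU, which has no therapy groups. The MBSR section takes instructor effects seriously enough to promise an analysis of them, yet the sample size counts every patient as an independent observation. For any positive ICC the stated power is then too high. The contrast most exposed is MBSR v FibroQoL, because both arms are clustered and because it is the comparison named in the first aim of the Background.

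The instructor sentence raises a separate problem. With each instructor leading exactly one group, a good or poor result in that group may come from the instructor, from the mix of patients, or from the period. A paper reporting an instructor effect from this design would report something that the design cannot isolate.

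**Working it through.** **Inputs.** d = 0.53, alpha = 0.05 (sidedness not stated), 60 per arm, 48 per arm after 20 % attrition (Participants); MBSR groups of 15, four instructors, one per group (MBSR section); four waves of 45, groups of up to 15 in both active arms (Procedure). The ICC is not given. I assume 0.01 to 0.10, the same in both active arms.

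**Structure.** 60 / 15 = 4 MBSR groups. With three equal arms, 45 / 3 = 15 patients per arm per wave, so one MBSR group per wave. The same arithmetic implies one FibroQoL group of 15 per wave, which is an inference and not stated.

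**Step 1: reproduce the stated power.** Two-sample noncentral t, independent patients, noncentrality d·√(n/2), df = 2n − 2.

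- n = 60: 0.53·√30 = 2.90. One-sided power 0.893; two-sided 0.821.
- n = 48: 0.53·√24 = 2.60. One-sided power 0.825; two-sided 0.729.

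The plan's 0.89 and 0.82 match the one-sided, independent-patient calculation. A three-arm ANOVA F test at n = 60 gives 0.854 or 0.734, depending on the pattern of means, and does not match.

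**Step 2: add clustering.** Design effect DE = 1 + (15 − 1)·ICC. The variance factor is VF = DE when both arms are clustered, and VF = (DE + 1)/2 against TAU. Noncentrality becomes 0.53·√(30/VF). One-sided alpha 0.05, patient-level df (118):

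| ICC | DE | MBSR v FibroQoL | VF v TAU | MBSR v TAU |
|---|---|---|---|---|
| 0 | 1.00 | 0.89 | 1.00 | 0.89 |
| 0.01 | 1.14 | 0.86 | 1.07 | 0.87 |
| 0.05 | 1.70 | 0.72 | 1.35 | 0.80 |
| 0.10 | 2.40 | 0.59 | 1.70 | 0.72 |

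At ICC 0.05 the 60 patients in a clustered arm carry the information of 60 / 1.70 = 35.3.

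- After 20 % attrition (12 per group, 48 per arm) DE at ICC 0.05 is 1 + 11·0.05 = 1.55. One-sided power for MBSR v FibroQoL is then about 0.67 (normal approximation), against the stated 0.82.
- With group-level degrees of freedom (eight groups, 6 df), power at n = 60 and ICC 0.05 is 0.63 one-sided and 0.46 two-sided. Even at ICC 0, 6 df gives 0.68 two-sided instead of 0.82.

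**Step 3: what can be learned about instructors.** In a model with arm, wave, MBSR instructor and MBSR group there are 12 parameters and the design matrix has rank 9: the three instructor columns and the three group columns are identical. Within the MBSR arm alone, wave plus instructor has 7 parameters and rank 4. What remains is one combined instructor/group contrast on 4 − 1 = 3 df. Its F test (3 and 56 df, with F scaled by 1 + 15·ICC/(1 − ICC)) has power of about 0.21 at ICC 0.05 and 0.38 at ICC 0.10.

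**Step 4: the conditional consequence for the analysis.** If a simple two-group comparison ignored the groups, the true two-sided size at nominal 0.05 would be 2·[1 − Φ(1.96/√VF)]. At ICC 0.01 / 0.05 / 0.10 this is 0.066 / 0.133 / 0.206 for MBSR v FibroQoL and 0.058 / 0.092 / 0.133 for MBSR v TAU. Simulation gave 0.066 / 0.135 / 0.208 and 0.060 / 0.093 / 0.134.

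**The case against.** The best defence is that this is a journal article. It names mixed models and stops there, and random effects, wave terms and a stratum covariate are commonly left to the full protocol or analysis plan. That stands. A reader might infer that the efficacy analysis treats patients as independent, but the document does not say so. The size figures in Step 4 therefore describe what would follow if groups were ignored, not a demonstrated defect. They also concern simple comparisons at one time point, not the planned model. Likewise, randomisation is stratified ("To balance the number of participants eligible for the biomarkers sub-study across the three arms, stratified randomisation will be performed"), and the absence of that stratum or of wave from the model description is missing detail and not an error.

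Four more limits are fair:

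- Four groups with one leader each is explicit for MBSR only. A reader might carry the instructor argument over to FibroQoL, but that section describes a team, so its clustering may come mainly from peers and its ICC could differ.
- A reader might conclude that instructor is confounded with wave throughout the trial. That holds only within the MBSR arm. FibroQoL and TAU run concurrently, so the wave main effect can be estimated from them if treatment-by-wave interaction is assumed absent. Instructor would still coincide with group.
- The instructor analysis is not impossible: a combined difference is estimable. What fails is attributing it to instructors.
- The power loss depends on an ICC that the document does not give. Only the direction is certain, for any positive ICC.

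The defence does not rescue the two statements at issue. The power figures are fixed in the article and reproduce only with independent patients, and no analysis plan can separate an instructor from the single group that the instructor led.

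**Conclusion.** The point holds for the power statement and for the instructor sentence. On the basis that reproduces 0.89, power for MBSR v FibroQoL is about 0.86 / 0.72 / 0.59 at ICC 0.01 / 0.05 / 0.10, and for MBSR v TAU about 0.87 / 0.80 / 0.72. These figures assume full groups of 15, four groups per active arm (inferred for FibroQoL), equal ICC in both active arms and patient-level df; group-level df lowers them further. The instructor claim fails from the layout of delivery alone, whatever the ICC. Whether the efficacy model accounts for therapy groups cannot be judged from this document. The matter should be settled before analysis but does not invalidate the trial.

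**What to change.** 1. Restate power over a declared ICC range for each pairwise contrast, with the number and size of therapy groups, the sidedness and the degrees of freedom used.
2. State in the mixed model a random intercept for therapy group in the MBSR and FibroQoL arms only, each TAU patient being a singleton, with Kenward-Roger or Satterthwaite degrees of freedom. Record each patient's group number.
3. Replace the instructor sentence with: *Instructor and therapy group coincide in the MBSR arm, and within that arm also coincide with wave; only their combined variation will be described.*

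The wording and data capture cost little. The statistical cost is real: clearly wider intervals, and power of about 0.46 two-sided for MBSR v FibroQoL at ICC 0.05 with 6 df. With four groups per active arm the group variance will also be poorly estimated: in the MBSR arm alone, an observed ICC of 0.05 would have a 95 % interval from about −0.03 to 0.62. The model should be presented with that limitation stated.

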
#### *Treatment as Usual control group* (TAU)

In Spain, treatment provided is mainly pharmacological and adjusted to the symptomatic profile of the patients with FMS. Counselling about aerobic exercise adjusted to patients’ physical limitations is usually provided.

#### *Active control group* (TAU + FibroQoL)

The FibroQoL is a psycho-educational programme for FMS patients based on a consensus document drawn up by the Health Department of Catalonia and shown to be cost-effective in a previous study [41]. This group-based programme is divided into two parts: The first part is led by three general practitioners, one rheumatologist and one psychologist. It includes updated information about pathophysiology, diagnosis, and management of FMS symptoms (4 sessions). The second part is led by a psychologist and includes training in self-hypnosis (4 sessions). In each of these sessions, a distinct self-hypnosis technique is explained and practiced. The goal of these techniques is to generate a state of deep relaxation, explore the sensations produced by one’s own body, achieve control over the body and pain, and imagine the one’s life in the future without pain. Many authors have emphasised the need to consider aspects of identity in order to understand the phenomena of chronic pain [49]. Therefore, it is especially useful to explore all the connections between the identity of a person, the perception of his/her body, and attitudes towards therapy in general. If we focus on the theory that each human activity is a process of creating meaning [50], people should assemble informal theories about, for instance, themselves, people or health. Their reactions to events such as bodily sensations or interpersonal experiences are mediated by their interpretations [51].

Some clinicians and scholars [51] highlight certain personality traits in patients with FMS, including an excessive sense of responsibility, extreme effort to please others, personal sacrifices made for others, little time set aside for themselves, and difficulty setting limits for others. These characteristics, as well as other difficulties showed by these patients, are discussed within the group and are part of the hypnotic inductions for each session. The group context has been considered an implementer of hypnotic response since the 18th century; the fact that someone in the group evidences minimal response raises expectations among the others and this reaction can increase the hypnotic susceptibility of all group members. The *naturalistic hypnosis* method requires that therapist is well trained in observation and should have a high degree of sensitivity when using the material provided by the patients. The reference model is Ericksonian hypnosis [52]. According to Erickson, a patient can use his/her own life experience, resources and prior learning therapeutically. The focus of Ericksonian hypnosis is to breakdown non-useful patterns and/or limit behaviours that prevent the construction of new meaning. Some typical properties of hypnosis facilitate this work, for example:Experience attention absorption: the person is absorbed in an aspect of context, stops paying attention to irrelevant stimuli.Changing the intensity of the experience: the sensorial and emotional experiences, linked to memories, are stronger.Willingness to experience: people during hypnosis, people are more amenable to unintentionally experience new perspectives; this feature is defined as suggestibility.Flexibility of Time-Space Relationship: experience of distortion of subjective time or temporary phenomena such as regression or projection into the future.Alteration of sensory experience: the person may experience changes in visual perception (e.g. *tunnel vision*), in hearing, in physical sensations (anesthesia, heaviness, lightness, size and position of body parts), loss of movement, or hands and/or fingers may occasionally move involuntarily (Table 2).

**Table 2 Tab2:** Session outlines for the FibroQoL group treatment protocol

Session	FibroQoL^a^
1	Introduction and general information. Patients’ Expectations. History and epidemiology of the syndrome. Common symptoms in FM. Physiological mechanisms involved in the genesis of pain.
2	Collect information on the goals of each patient, explain differences between physical and emotional pain, clarify differences between hypnosis and self-hypnosis, administer hypnotisability test, hypnosis “safe place”.
3	Diagnosis and prognosis. Pharmacological and non-pharmacological treatments. Current model of health care in Catalonia and units specialised in the treatment of FM patients.
4	Discussion of goals and the difficulties that obstruct them, emphasize common personality characteristics, highlight exceptions to the problem, hypnosis “candle and bubbles”.
5	Strategies to increase self-esteem and regulate emotions. Pain experience and recurrent invalidation. Social support from family and close friends.
6	Exploration of possible changes, difference between acute and chronic pain, hypnosis: “imagination of a journey”.
7	Reviews the goals, ask for a future possible change (the miracle question), commitment to consolidation of the changes, hypnosis: “watch a photo album”.
8	Benefits of physical exercise in FM and closing remarks

^a^NOTE: The current FibroQoL version contains eight 2-h sessions instead of 9. The multidisciplinary team decided to dismantle the FibroQoL program, eliminating the session focused on “Holistic Medicine” because it contained some information about meditation/mindfulness. Thus, both MBSR and FibroQoL are structurally equivalent, which provides a comparison of MBSR with an intervention that matches MBSR in non-specific factors, but does not contain mindfulness ingredients

